### Statistical analyses

All statistical analyses will be performed using STATA statistical software (STATA 10; Statistical data analysis; Stata Corp; College Station; Texas, USA). Baseline and descriptive data between the groups will be analysed with one-way ANOVA. Binary categorical data will be analysed for variability between the groups using logistic regression. Parametric longitudinal data analysed via two-factor (group, time) analysis of variance (ANOVA) with repeated measures on time using general linear modeling. Weekly physical activity (MET.min^-1^) will be analysed via general linear modelling. Where statistically significant differences are identified, post hoc testing will be performed using Holms tests to locate the means that are significantly different. Statistical significance will be set at p < 0.05.

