**Methods and design:**

This is a randomised, controlled clinical trial. A total of 72 hemodialysis patients will be randomised to receive either six months of intradialytic exercise training, home-based exercise training or usual care. Intradialytic patients will undergo three training sessions per week on a cycle ergometer and home-based patients will be provided with a walking program to achieve the same weekly physical activity. Primary outcome measures are six-minute walk distance (6 MWD) and aortic pulse wave velocity (PWV). Secondary outcome measures include augmentation index, peripheral and central blood pressures, physical activity and self-reported health. Measures will be made at baseline, three and six months.

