### Withdrawal from study

Subjects will be withdrawn from the study at their request, without prejudice, as documented and explained at the time of consenting. Patients who withdraw will be invited to consent to follow-up testing for the remainder of the trial to enable an intention to treat data analysis.

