### Sample size calculation

Data from other studies indicates that 6 MWD has the highest variability of the two primary outcome measures (mean ± SD; PWV = 11.1 ± 3.2 [29], 6 MWD = 347 ± 147 m[30]). We assume that this will also mean that changes in 6 MWD will be more variable than changes in PWV. We then assume that a 10% improvement in 6 MWD will be clinically significant. Therefore, with alpha = 0.05, and beta = (1-0.1 = 0.9) we require 17 subjects per group. Allowing for a 20% withdrawal rate we aim to recruit 20 patients per group.

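### The named repeated-measures ANOVA does not properly use patients who lack a 6-month value, so it is a poor match for the intention-to-treat aim and the 20% withdrawal allowance

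*Protocol article*

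**What the plan says.** Three statements in the protocol article bear on patients who leave.

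- **Withdrawal from study:** "Patients who withdraw will be invited to consent to follow-up testing for the remainder of the trial to enable an intention to treat data analysis". Outcomes after withdrawal are sought, but only from those who agree.
- **Sample size calculation:** "Allowing for a 20% withdrawal rate we aim to recruit 20 patients per group". This follows a requirement of 17 per group.
- **Statistical analyses:** "Parametric longitudinal data analysed via two-factor (group, time) analysis of variance (ANOVA) with repeated measures on time using general linear modeling". 6 MWD and aortic PWV are continuous outcomes measured at baseline, 3 and 6 months, so this is the method for both primary outcomes.

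The statistical section does not say whether the model is fitted with one record per patient or one per visit, and it does not say that incomplete patients are excluded.

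**The concern.** Repeated-measures ANOVA is designed for complete sets of visits. The protocol expects some patients to leave, and those who decline testing will have gaps. A patient seen at baseline and month 3 carries information about the likely month-6 result, and an intention-to-treat analysis should use it. The named method either discards it or gives it a fixed weight that is right only under a special correlation pattern.

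This matters because the two exercise arms are run very differently. One is supervised at three sessions a week. The other is unsupervised, with a telephone call every two weeks. The protocol itself expects patients to be more likely to meet activity guidelines when supervised, so reasons for leaving could differ by arm. If home-based patients who progress poorly by month 3 leave more often, those who remain look better than the arm as randomised. The intradialytic versus home-based contrast, which is the stated hypothesis, then moves in favour of home-based training.

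**Working it through.** **1. The plan's own figures.** The withdrawal step takes 17 to 20 per group. Dividing gives 17/0.8 = 21.25, so 22. Multiplying gives 17 × 1.2 = 20.4, so 21. The stated 20 is close to both. If every withdrawer declined testing, 20 × 0.8 = 16 per group would have a 6-month value, so 4 per group (12 of 60) would lack one. That is the upper figure for loss due to withdrawal. The target effect is 10% of 347 m = 34.7 m.

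**2. What each fit does with a patient who lacks month 6.** Let d0, d1, d2 be the patient's deviations from the arm means at 0, 3 and 6 months, with equal variances. The quantity at risk is the change d2 - d0, when loss depends on the observed d1 - d0.

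- Listwise fit: the patient is dropped, so the observed d1 - d0 gets weight 0.
- Long form with patient effects: the missing d2 is in effect replaced by (d0 + d1)/2. The change is then (d0 + d1)/2 - d0 = 0.5 × (d1 - d0), a weight of 0.5. A baseline-only patient adds nothing to group-by-time.
- Correct weight: Cov(d2 - d0, d1 - d0) / Var(d1 - d0).
  - Equal correlations ρ: (1 - ρ) / [2(1 - ρ)] = 0.5, so the long form is right.
  - Correlation decaying with time (AR(1)): (1 - ρ²) / [2(1 - ρ)] = (1 + ρ)/2. At ρ = 0.85 this is 0.925, so the long form removes only 0.5/0.925 = 54% of the listwise bias.

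The protocol gives no correlations between visits, so neither pattern can be taken as given.

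**3. Size, by simulation.** From the protocol: SD 147 m, 20 per arm, visits at 0, 3 and 6 months, a 34.7 m gain in both exercise arms (true difference 0), and 20% loss. Assumed: a quarter of losses before month 3 at random and three quarters after it; late loss in the home-based arm weighted by 0, 1 or 2 on the log scale per SD of worse month-3 change; loss at random in the other arms; adjacent-visit correlation 0.70 to 0.95.

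Bias in intradialytic minus home-based 6 MWD at month 6 (listwise / long form / likelihood), with Monte Carlo standard error 0.4 to 1.4 m:

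- AR(1) 0.85, weight 1: -12.3 / -6.2 / -0.9 m
- AR(1) 0.85, weight 2: -17.9 / -9.3 / -1.6 m
- Equal correlation 0.85, weight 1: -5.6 / 0.2 / -0.2 m
- Weight 0: no bias beyond simulation error for any method

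The long-form to listwise ratio in the AR(1) rows is 6.2/12.3 = 0.50 and 9.3/17.9 = 0.52. Step 2 predicts (0.925 - 0.5)/0.925 = 0.46, so the mechanism and the simulation agree.

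Over all settings at SD 147 m, listwise bias runs from about -3 to -22 m, long-form bias from 0 to about -9 m, and likelihood bias is at most about 2 m in size. The most extreme setting (AR(1) 0.70, weight 2), run separately with 800 replicates, gave -23.9 / -11.1 / -1.8 m. The upper ends are therefore good to about 2 m.

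**4. Sensitivity to the SD of change.** The 17 per group implies, two-sided, an SD of change of 34.7 × √(17/2) / (1.960 + 1.282) = 31.2 m, which is far below what SD 147 m with correlation 0.70 to 0.95 gives. At 31 m, with 20% missing, listwise bias is -2.1 to -4.9 m and long-form bias about 0 to -2.4 m. If half of the withdrawers accept testing (10% missing), these become -1.4 to -3.2 m and about 0 to -1.6 m. Whether 31 m is credible is a separate sample-size question.

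**The case against.** The strongest reply is that the protocol's route to intention to treat is to keep testing people after withdrawal. A withdrawer who accepts has a real 6-month value, and the ANOVA uses it. A reader might infer that the method cannot score withdrawers at all, that 20% of patients will be missing, that the primary result is therefore a completer analysis, or that the ANOVA and the intention-to-treat aim are incompatible. The document supports none of these. The 20% is a withdrawal rate, not a missing-data rate. The completer reading holds only for a listwise fit, which the text does not specify. In one simulated example a long-form fit kept about 200 of 216 rows and estimated 0.42 against a true 0.40, while completers alone gave 0.52. That example was generated with equal correlations, where the long form is expected to work.

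It is also fair that nothing in the document establishes outcome-related loss in the home-based arm alone, and that without it there is no bias. Nor does a mixed model settle what to do about death, inability to walk, or leaving haemodialysis (which removes the pre-dialysis setting for PWV).

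Finally, rules for missing data are commonly left to an analysis plan, and their absence from an article is no fault. That disposes of any complaint about silence. It does not dispose of this point, because the article does fix a method, and a missing-data rule added later would not make that method weight the month-3 value correctly.

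**Conclusion.** The point holds as a choice of method that should be improved, not as a contradiction. With patients expected to leave and intention to treat as the aim, a repeated-measures ANOVA is the weaker tool. At best it is right under equal correlations, and at worst it drops incomplete patients.

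Under the assumed arm-specific loss, the bias in 6 MWD is about -2 to -22 m listwise, which is 6% to 63% of 34.7 m. In long form it is 0 to about -9 m, up to 26%. A likelihood-based model stays within about 2 m. The size rests wholly on that dropout assumption, on all or most withdrawers declining testing, and on unstated correlations between visits. The low end of the listwise range belongs to the small SD of change implied by 17 per group, and the high end to SD 147 m with weak correlation. If loss is unrelated to outcome, the bias is zero. No figure was derived for PWV; the mechanism is the same.

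**What to change.** In Statistical analyses, replace the repeated-measures ANOVA for 6 MWD and aortic PWV with a likelihood-based mixed model for repeated measures. Use baseline, 3 and 6 months as the response with an unstructured covariance. Include all available values of all randomised patients, including tests done after withdrawal, and analyse by randomised arm. State that this is the intention-to-treat analysis that the withdrawal section aims at.

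The cost is a few lines of text and a different model command, with no extra patients, visits or staff. There are two limits. The model assumes data are missing at random given the observed values, and with about 20 per arm it needs a small-sample degrees-of-freedom correction. The sponsor should confirm that the named software version offers both the covariance structure and the correction.

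Sensitivity analyses, such as shifting missing 6-month values in the exercise arms or ranking deaths and patients unable to walk worst for 6 MWD, are optional detail for the analysis plan.

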### Primary objectives and primary outcome measures

The primary objectives are to compare the effects of supervised intradialytic and home-based exercise training on physical function and arterial stiffness. The primary outcome measures will be outlined below. The hypothesis is that supervised training will be superior to home-based training because the patients will be more likely to meet physical activity guidelines when supervised.

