## Discussion and conclusion

The objective of this trial is to compare a supervised intradialytic training program with a home-based exercise program and usual care. The results of this study will help determine the efficacy of home-based exercise training in hemodialysis patients which may be a more cost effective way of conducting an exercise program as many dialysis units are too crowded and busy to allow for intradialytic exercise programs. This may help in the development of exercise guidelines for dialysis patients. The study will also assess whether the various exercise interventions impact on arterial stiffness a surrogate marker of cardiovascular morbidity in these patients.

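### The primary comparison, intradialytic against home-based training, is reached only conditionally through an omnibus group-by-time ANOVA with no decisive effect fixed, and baseline is tested between arms but not used as a covariate

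*Protocol article*

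**What the plan says.** Under Primary objectives and primary outcome measures, the protocol article sets a pairwise aim: "The primary objectives are to compare the effects of supervised intradialytic and home-based exercise training on physical function and arterial stiffness". It gives that aim a direction: "The hypothesis is that supervised training will be superior to home-based training". The Discussion and conclusion adds a claim that needs the usual-care arm: "The results of this study will help determine the efficacy of home-based exercise training in hemodialysis patients".

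Statistical analyses gives the model for the longitudinal outcomes: "Parametric longitudinal data analysed via two-factor (group, time) analysis of variance (ANOVA) with repeated measures on time using general linear modeling". The follow-up rule is: "Where statistically significant differences are identified, post hoc testing will be performed using Holms tests to locate the means that are significantly different". On baseline it says: "Baseline and descriptive data between the groups will be analysed with one-way ANOVA". Neither the decisive effect (group, time or interaction) nor a between-arm contrast or primary visit is named, and baseline is not mentioned as a covariate. The Abstract and Interventions sections place measurements at baseline, three and six months.

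**The concern.** The hypothesis concerns one pair of arms. The analysis first asks a general question about three arms and several visits, and turns to pairs only if that question gives a significant answer. Three consequences follow.

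- **The trigger is not fixed.** A two-factor ANOVA yields F tests for group, time and interaction. Only the interaction clearly bears on treatment when baseline is one of the visits. As written, a change shared by all arms, such as learning the walk test, could also open the post hoc step.
- **The target of the post hoc tests is not fixed.** Locating means that differ can be read as comparing visits within an arm. That invites the argument that one arm improved and another did not, in place of a between-arm difference in change.
- **Baseline is used where it helps least.** Testing it between randomised arms does nothing for the treatment estimate. As a covariate it reduces variance and corrects chance imbalance in small arms.

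At stake are power for the stated hypothesis and protection against choosing the effect, pair or visit after seeing the data.

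**Working it through.** **Inputs from the protocol article.** There are three arms and three visits. The sample size section requires 17 per group, and significance is set at p < 0.05. The plan states no power for the comparison of the two exercise arms under this analysis, so there is no figure of that kind to reproduce. I take 17 per arm as given. It does not follow from the quoted mean and SD of 6 MWD alone, which is a separate matter.

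**Assumptions.** Correlation r between any two visits is 0.5 to 0.9 (compound symmetry), because the article gives none. Data are complete. Only the intradialytic arm improves, linearly to 6 months. The effect size is set so that a single baseline-adjusted 6-month contrast at two-sided 0.05 has about 90% power.

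**Gated route.** The interaction F test has 4 and 2 × (51 − 3) = 96 degrees of freedom. If p < 0.05, Holm is applied to the three pairwise differences in 0–6 month change. This reading is kind to the plan. If the Holm family were all nine group-by-visit means, it would contain 9 × 8 / 2 = 36 pairs.

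**Power for intradialytic against home-based** (4000 runs per correlation; 6-month ANCOVA stands in for the mixed model, to which it is nearly equivalent with complete data):

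| r | Gate, then Holm on change | Holm on change, no gate | Holm on three baseline-adjusted contrasts |
|---|---|---|---|
| 0.5 | 66% | 71% | 83% |
| 0.7 | 72% | 76% | 83% |
| 0.8 | 74% | 78% | 82% |
| 0.9 | 78% | 82% | 82% |

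A separate run gave 66, 72, 73 and 78% for the gated route and 83, 83, 82 and 83% for the adjusted contrasts. A third, with the direct contrast at about 89%, gave 63, 68, 73 and 76% for the gated route.

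**Splitting the gap.**
- Gate: second column minus first is 71 − 66 = 5 points at r = 0.5 and 82 − 78 = 4 at r = 0.9. Across runs it is about 3–5.
- Like-for-like gap, with Holm on both sides: 83 − 66 = 17 points at r = 0.5 and about 4–5 at r = 0.9.
- Holm itself: about 90% (tested alone) minus about 83% is about 7 points.

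**Baseline adjustment.** The variance of a change score relative to the baseline-adjusted estimate is 2(1 − r)/(1 − r²) = 2/(1 + r). This gives 2/1.5 = 1.33, 2/1.7 = 1.18, 2/1.8 = 1.11 and 2/1.9 = 1.05 at r = 0.5, 0.7, 0.8 and 0.9. For a 34.7 m advantage (10% of 347 m) with SD 147 m and 17 per arm, the change-score and adjusted contrasts, each tested alone, have 56% and 58% power at r = 0.95, and 84% and 85% at r = 0.975.

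**Group main effect.** If baseline is a level of time and the effect d builds linearly, the main effect averages (0 + d/2 + d)/3 = d/2, half of the 6-month effect.

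**How often the gate opens if any of the three F tests counts.** With no effect at all the simulated rate is 14.2%, in line with 1 − 0.95³ = 14.3%. With a 0.3 SD change shared by all arms it is 51, 72, 88 and 99% at r = 0.5, 0.7, 0.8 and 0.9.

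**The case against.** The strongest defence is that this is a condensed article. Contrast lists, covariates, covariance structure and primary visit are commonly left to an analysis plan, which is not shown. That stands for mere absence. It does not cover what the article does fix: a method, a trigger and a follow-up rule that do not match its own hypothesis.

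A reader might infer four stronger points, none of which the document supports.

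- **That the hypothesis is never tested directly.** With three arms, Holm tests would ordinarily include intradialytic against home-based. The accurate statement is that the pair is reached only after a significant result and is not named as primary.
- **That baseline is ignored.** Baseline as a level of time is inferred from the visit schedule; the analysis section does not say so. On that natural reading the interaction already compares changes from baseline, so what is lacking is covariate adjustment. At high correlations this is a small loss of efficiency.
- **That 14%, or 51–99%, is a rate of false treatment claims.** These are rates of opening the post hoc step. A time effect followed by tests of time means claims nothing about treatment, and the article does not say it would be read that way.
- **That incomplete visits will be dropped.** The text leaves this open. Patients who withdraw are invited to further testing "to enable an intention to treat data analysis".

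Setting the gated route against 90% also overstates the loss, because 90% belongs to one contrast with no multiplicity adjustment. If home-based training gains half as much as intradialytic, the gate costs nothing and the like-for-like gap at r = 0.9 is about 1 point.

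**Conclusion.** The concern holds in this limited form. The stated analysis reaches the primary comparison only conditionally, leaves open which effect is decisive and whether within-arm comparisons count, and uses baseline for significance tests but not as a covariate.

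With 17 per arm and only the intradialytic arm improving, power is about 66–78% as planned. It is about 83% with three baseline-adjusted contrasts under Holm, and about 90% if the primary contrast is tested first alone. Much of the avoidable loss at r = 0.5 is the missing adjustment; at r = 0.9 it is nearly all the gate. These figures rest on assumed correlations, compound symmetry, complete data and a linear effect. The direction is secure; the size depends on r and on how much the home-based arm gains. The change is worth making, but the planned analysis is not invalid.

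**What to change.** For 6 MWD and for aortic PWV, replace the omnibus-gated ANOVA with a likelihood-based mixed model of the 3- and 6-month values. Fixed effects are baseline value, visit, group and group × visit, and all available visits of all randomised patients are used. Name the intradialytic minus home-based difference in change at 6 months as the primary contrast, reported with a 95% confidence interval and no preceding omnibus test.

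State one multiplicity rule for this contrast and the two against usual care, which the efficacy statement about home-based training needs. Choose one of these, not both:

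- Holm over the three contrasts; or
- intradialytic against home-based first at 0.05, then the usual-care contrasts in a stated fixed order.

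Tabulate baseline descriptively and drop its significance tests.

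The cost is analysis wording, slightly more programming and one or two degrees of freedom, with no new data or patients. Holm leaves the primary contrast at about 83% power in the scenario above. The fixed order restores about 90%, but the usual-care contrasts can then be claimed only if the first succeeds.

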### Visits two and three

These visits will occur at approximately three and six months after baseline. Measures and the sequence of these measures will be identical to the baseline visit.

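### If correlation falls with time between visits, the classical repeated-measures ANOVA understates the error of the baseline-to-6-month arm contrast; give each contrast its own error variance

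*Protocol article*

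**What the plan says.** The Statistical analyses section fixes one model for the parametric longitudinal outcomes: "Parametric longitudinal data analysed via two-factor (group, time) analysis of variance (ANOVA) with repeated measures on time using general linear modeling". It continues: "Where statistically significant differences are identified, post hoc testing will be performed using Holms tests to locate the means that are significantly different". The threshold follows: "Statistical significance will be set at p < 0.05". These outcomes include both primaries, 6 MWD and aortic PWV.

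The time factor has three levels. The abstract states "Measures will be made at baseline, three and six months", and the section on visits two and three agrees: "These visits will occur at approximately three and six months after baseline". The group factor also has three levels: "six months of intradialytic exercise training, home-based exercise training or usual care". The stated hypothesis is that supervised intradialytic training is superior to home-based training.

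The article names no covariance structure, no error term for the post hoc contrasts and no sphericity correction. It gives no correlation between visits and no SD of change.

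**The concern.** With three visits there are three changes: baseline to 3 months, 3 to 6 months, and baseline to 6 months. The classical univariate ANOVA assumes that all three have the same variance (sphericity) and uses their average as the error for each. Measurements further apart in time often correlate less. The baseline-to-6-month change is then the most variable of the three, and averaging it with the two shorter changes understates its error. The 3-month contrast is affected in the opposite direction. None of this needs missing data.

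At stake is the contrast over the whole six-month intervention between the two exercise arms, which is the trial's stated hypothesis. If its standard error is too small, supervised training could be declared superior to home-based training more often than the nominal 5% allows, and the article intends the results to inform exercise guidelines.

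**Working it through.** **Inputs from the article.** Three arms, three visits and a threshold of 0.05 (taken as two-sided). I use 20 per arm from the sample size section. The abstract's total of 72 would give 72/3 = 24 per arm under equal allocation. The result hardly depends on this: with correlations 0.8, 0.8, 0.64, simulation gave 9.7% to 10.0% for 17, 20 and 24 per arm.

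**Inputs assumed.** The between-visit correlations, with equal variance at each visit (set to 1) and complete data.

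**Formulas.** A change between two visits with correlation r has variance 2(1 − r). Twice the pooled within-patient mean square estimates the mean of the three change variances. So

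- R = Var(baseline-to-6-month change) / mean of the three change variances
- standard error used / true standard error = 1/√R
- real two-sided error of one contrast = 2[1 − Φ(1.96/√R)]

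**Nominal figure first.** With all correlations 0.8, the change variances are 0.40, 0.40 and 0.40, R = 1 and the error is 5.0%. The plan's 5% is reproduced under sphericity.

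**One decaying case in full.** With correlations 0.8, 0.8 and 0.8² = 0.64, the change variances are 0.40, 0.40 and 0.72, with mean 1.52/3 = 0.507. R = 0.72/0.507 = 1.42, 1/√R = 0.84, and the error is 2[1 − Φ(1.96/1.192)] = 10.0%.

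| Correlations (0–3, 3–6, 0–6 months) | Change variances | R | 1/√R | One unadjusted contrast |
|---|---|---|---|---|
| 0.80, 0.80, 0.80 | 0.40, 0.40, 0.40 | 1.00 | 1.00 | 5.0% |
| 0.85, 0.85, 0.80 | 0.30, 0.30, 0.40 | 1.20 | 0.91 | 7.4% |
| 0.85, 0.85, 0.75 | 0.30, 0.30, 0.50 | 1.36 | 0.86 | 9.3% |
| 0.70, 0.70, 0.49 | 0.60, 0.60, 1.02 | 1.38 | 0.85 | 9.5% |
| 0.80, 0.80, 0.64 | 0.40, 0.40, 0.72 | 1.42 | 0.84 | 10.0% |
| 0.90, 0.90, 0.81 | 0.20, 0.20, 0.38 | 1.46 | 0.83 | 10.5% |

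Still milder decay (0.85, 0.85, 0.82) gives R = 0.36/0.32 = 1.125 and 6.5%. In an example where month 3 is the noisiest visit, R = 0.43 and the error is 0.3%, so the contrast is conservative.

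**The procedure as written.** I simulated 20,000 trials with 20 per arm. The group-by-time interaction had to reach p < 0.05, and Holm was then applied to the three arm pairs on the baseline-to-6-month change with the pooled error.

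- *No arm differs.* The interaction test rejects in about 6% under decaying correlation. A given pair rejects in about 2% (0.85, 0.85, 0.80) to 3% (0.9, 0.9, 0.81), and in about 1% with equal correlations.
- *Both exercise arms improve equally over usual care.* The gain was about 1.1 SD of change at month 6, roughly what 17 per group detects with 90% power, and half of that at month 3. The false-positive rate for intradialytic versus home-based is about 4% with equal correlations, 6.5% with 0.85, 0.85, 0.80, 8.5% with 0.85, 0.85, 0.75, and 9% to 9.7% for the three faster-decaying patterns.
- *Usual care differs from both by 1 SD of the outcome at month 6.* The rates are 9.2% (0.8, 0.8, 0.64) and 10.3% (0.9, 0.9, 0.81), against 4.9% with equal correlations.

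When exercise works, the interaction test nearly always opens the gate (92% to 97% of runs in the second scenario). Usual care is usually rejected against both exercise arms, and Holm then tests the remaining true-null pair at the full 5%.

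**With the change's own error variance.** A single unadjusted test stays at 4.7% to 5.2% under all these patterns.

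**The case against.** The article never says that post hoc contrasts use a pooled error. That is inferred from the name of the method, and a condensed article may leave error terms and sphericity handling to a fuller document. This stands, and the point must be conditional. The article does name the model, however, and the model's standard form carries the assumption. A sphericity correction of the Greenhouse–Geisser type would not settle the matter, because it adjusts the omnibus F test and leaves the pooled standard error of the contrasts unchanged.

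A reader might infer that the 6-month standard error is too small in this trial, or that the planned procedure has a 10% error rate. The documents support neither. There is no excess with equal correlations, and the direction reverses if month 3 is the noisiest visit. The size rests entirely on assumed correlations. When no arms differ, the gate and Holm hold a given pair at about 2% to 3%, and the interaction test itself is barely affected. What the gate and Holm do not protect is the comparison of the two exercise arms when both beat usual care.

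The article also does not single out the baseline-to-6-month change contrast; it speaks of locating differing means. A comparison of arm means at one visit includes between-patient variance and has a different error structure, which the figures here do not cover.

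**Conclusion.** The point holds in conditional form. The named ANOVA, in its classical form, relies on sphericity over three visits. If correlation declines with the gap between visits and post hoc change contrasts use the pooled error, the 6-month contrast has a standard error about 9% to 17% too small. This follows from 1/√R of 0.91 to 0.83 in the table. The realistic consequence concerns the main hypothesis when exercise works: up to about twice the nominal error for intradialytic versus home-based training. The conclusion assumes decaying correlation, equal variances across visits and equal arms. The mechanism is certain and the size is not, because the article gives no between-visit correlations. This is an inexpensive improvement to the analysis section and not a demonstrated error in the trial.

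**What to change.** In Statistical analyses, replace the two-factor repeated-measures ANOVA for 6 MWD, aortic PWV and the other longitudinal outcomes with a repeated-measures linear model that has an unstructured visit covariance. Alternatively, keep the ANOVA and state that each between-arm change contrast is tested with the error variance of that change, not the pooled within-patient mean square. The Holm adjustment can stay as written.

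The change is one sentence. At 20 per arm, the error degrees of freedom for the 6-month contrast fall from (60 − 3) × (3 − 1) = 114 to 60 − 3 = 57. If correlation does decay, the 6-month interval will be somewhat wider, and correctly so.

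### The stated 90% power makes no allowance for the Holm step through which the plan tests one arm against another

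*Protocol article*

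**What the plan says.** The protocol article is the only document shown.

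- **Sample size calculation.** It cites a 6-minute walk distance with mean 347 m and SD 147 m. The target is set by "We then assume that a 10% improvement in 6 MWD will be clinically significant", and the result is "with alpha = 0.05, and beta = (1-0.1 = 0.9) we require 17 subjects per group" (the 0.9 is evidently the power). No test, contrast, sidedness or multiplicity adjustment is given.
- **Statistical analyses.** Longitudinal outcomes go into a two-factor (group, time) repeated-measures ANOVA. Only after a significant result are means compared: "post hoc testing will be performed using Holms tests to locate the means that are significantly different". The overall level is 0.05. The section does not say which ANOVA effect opens the gate.
- **Primary objectives and primary outcome measures.** "The hypothesis is that supervised training will be superior to home-based training". This is a contrast between two of the three arms.

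**The concern.** The contrast that carries the hypothesis has two hurdles to clear: a significant ANOVA and then a Holm step. With three arm contrasts the Holm thresholds are 0.05/3 = 0.0167, 0.05/2 = 0.025 and 0.05. The planning figure reflects neither hurdle. If its alpha of 0.05 was meant for a pair of arms, the trial is planned at one level and tested at a stricter one, so readers are told of more power than the analysis has. If it was meant for the overall test, the supervised-versus-home contrast has no stated power at all.

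**Working it through.** **1. The plan's own figure.** Inputs from the sample size section: difference 10% of 347 = 34.7 m, SD 147 m, alpha 0.05 (two-sided assumed), power 0.90.

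n per group = 2 × (1.960 + 1.282)² × (147/34.7)² = 2 × 10.51 × 17.95 ≈ 378.

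The stated 17 is not reproduced. One-sided testing gives 308, and paired or one-sample forms at 90% power give 154 to 189. With SD 147 m, 17 per group has about 10% power. No SD of change is printed.

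**2. The effect that 17 per group implies.** Setting two-sample t-test power to 0.90 at n = 17 and alpha 0.05 gives d = 1.147, that is, an SD of 34.7/1.147 ≈ 30.3 m (31.2 m by the normal approximation). Read as an SD of change, 31.2 m implies a baseline-to-follow-up correlation of 1 − (31.2/147)²/2 ≈ 0.98. The power figures in steps 3 and 4 are conditional on this d. They measure the effect of the testing procedure and do not endorse the effect size.

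**3. Power at fixed levels** (noncentral t, n = 17, d = 1.147):

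- alpha 0.05: 0.900
- alpha 0.025: 0.834
- alpha 0.0167: 0.788

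The last is a lower bound for Holm without the gate, because only the smallest of the three p-values must meet 0.0167.

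**4. The sequence in three arms.** Simulation of 200,000 trials, 17 per arm, pooled variance, one outcome at one time point, gate = 2-df F test at 0.05. Power for supervised versus home:

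| True means (supervised, home, usual care) | Gate, pairs at 0.05 | Gate, then Holm |
|---|---|---|
| d, 0, 0 | 0.883 | 0.831 |
| d, d/2, 0 | 0.365 | 0.282 |
| 2d, d, 0 | 0.906 | 0.903 |

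In the first row, Holm with no gate gives 0.832. A gate can only remove rejections, so no choice of gate lifts Holm over three contrasts above about 83% there. In the second row the contrast is only d/2, so most of the shortfall from 90% comes from the smaller effect; Holm accounts for about 8 points.

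**5. Familywise error for the three pairs.** Gate plus pairs at 0.05: 0.050 with all arms equal and 0.050 with one equal pair. Gate plus Holm: 0.042 and 0.039. The reason is that with three arms, once they are not all equal, at most one pairwise null can be true. A 2-df gate at 0.05 followed by pairs at 0.05 is therefore a closed procedure.

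**6. Does this carry over to the gate as written?** No. A group-by-time interaction with three arms and three visits has (3 − 1) × (3 − 1) = 4 df. It can be significant because arms differ at 3 months while all three are equal at 6 months. With an effect at 3 months only, 6-month pairs tested at 0.05 behind the interaction gate have familywise error of about 12%, against about 4.5% with Holm.

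**The case against.** The case on the other side is substantial, and much of it stands.

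- **Holm is redundant after the ANOVA.** A reader might infer this from the three-arm argument. The document does not support it: the planned gate is a group-by-time analysis, and step 6 shows Holm doing real work behind it.
- **Type I error is at fault.** It is not. Holm is valid and conservative.
- **Holm runs over all nine group-by-time means, with far stricter thresholds.** The wording does not exclude this, but nothing states it. The post hoc family is the kind of detail an article leaves to an analysis plan, so nothing is claimed on that basis.
- **Power falls to 79%.** That is the first-step bound. The simulated loss is about 5 points with one arm differing, 8 in the intermediate case and almost nothing when the arms are widely spaced.
- **The pairwise reading of the planning alpha is an inference.** This stands, and the conclusion is conditional on it.
- **More patients may be available than 17 per arm.** The abstract has "A total of 72 hemodialysis patients will be randomised to receive either six months of intradialytic exercise training, home-based exercise training or usual care". With equal allocation (assumed) that is 24 per arm, or about 19 after 20% loss. At the same d, with one arm differing, power is then 92% without Holm and 88% with it. The sample size section, however, aims for 20 per group.
- **The larger fault is that 17 does not follow from SD 147 m.** True. On the printed inputs power is about 6% without Holm and 5% with it, so the choice hardly matters there. But any corrected calculation must still use the procedure that will be applied.

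**Conclusion.** The point holds as a mismatch between planning and analysis. If alpha 0.05 was planned for a pairwise contrast, the stated 90% is not what an ANOVA gate followed by Holm delivers in general. At d ≈ 1.15 with 17 evaluable per arm, supervised-versus-home power is about 83% when only supervised training differs from the rest, and about 28% instead of 37% if home training keeps half the gain. Only a wide, even spacing of the arms restores about 90%.

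These figures assume two-sided tests, Holm over three arm contrasts at one time point, a 2-df gate in the simulation, and an effect size back-solved from the 17. Holm becomes unnecessary only if the gate is changed to a 2-df three-arm test at the same time point as the pairs. It is a moderate point, cheap to settle, and secondary to the unsupported 17 per group.

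**What to change.** Choose one of two routes for each primary outcome.

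1. **Change the gate and drop Holm.** Name the 2-df three-arm comparison at 6 months, at 0.05, as the gate. If it is significant, test the three pairwise 6-month contrasts each at 0.05. Familywise error stays at 5% per outcome (not across the two primary outcomes), and power rises by 5 to 8 points in the first two configurations above. The cost is a narrower gate: a difference confined to 3 months no longer opens it. The gate itself still costs a little, 88% rather than 90% when one arm differs, so the power statement should be for this procedure.
2. **Keep Holm.** Limit it to the three 6-month arm contrasts and restate the power in the sample size section for that procedure. The cost is a less favourable stated figure, or more patients.

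Under either route, state which contrast and test the sample size is for, and give the SD of change used, since no restated figure can be checked without it. The choice of route needs new wording in the two sections only. Correcting the SD may change the required number, and that is a separate and larger matter.
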